### Outcomes

The primary outcome will be the change on the MADRS, a 10-item, validated, observer-administered scale of depression severity, which has been extensively used in trials of depression treatment [34]. Investigators will use a structured interview guide when administering the MADRS to improve inter-rater reliability [35].

Secondary outcomes will include the change on the Quick Inventory of Depressive Symptomatology (QIDS-SR-16), a 16-item, participant-administered scale of depression severity, and the World Health Organization Disability Assessment Schedule (WHODAS 2.0), a 12-item measure of functional impairment [36,37]. Cognitive impacts of treatment will be assessed using the Screen for Cognitive Impairment in Psychiatry (SCIP) [38]. The SCIP has been well validated as a tool for measuring cognitive change in patients with depression and other psychiatric illnesses; is brief and relatively simple to perform; and includes a verbal list learning task, working memory test, verbal fluency test, delayed learning task, and visuomotor tracking test. Exploratory analyses will investigate the effect of treatment on language abilities by change in performance on an auditory lexical decision task, in which participants must differentiate real from fictitious words [39,40]. An exploratory acoustic and semantic corpus analysis will also be conducted on the recorded entrance and exit interviews.

Treatment-related manic or hypomanic switches will be captured using the Young Mania Rating Scale, an 11-item observer-administered scale of mania intensity [41]. Other treatment-related side effects will be measured using a scale derived from a systematic review of tDCS-related adverse events [42]. This scale has the benefit of asking participants to comment on the relatedness of their symptoms to their treatment and may help to distinguish between the likely side effects of tDCS and symptoms participants had before the intervention. It has also been used in other randomized control trials evaluating tDCS [43]. In addition, side effects that may be secondary to concurrent medication use will be captured using the Frequency, Intensity, and Burden of Side Effects Rating Scale and the Patient-Rated Inventory of Side Effects Scale [44,45]. Side effects captured through the use of the aforementioned scales will be summarized in an adverse events form, with additional documentation completed on any adverse events deemed to be serious in nature.

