### Data Collection

Measurements for most scales will be conducted at the beginning of the trial (T0), after every 10 sessions (T10, T20, and T30), and 1 month after trial completion (T60; Table 1). Trained psychiatrists, psychiatric residents, and/or medical students will complete all assessments. Data will be collected directly using the REDCap electronic data capture tools.

Recorded entrance and exit interviews will be stored in an encrypted database and have identifying information stripped from them on a rolling basis. This database may then be analyzed in future studies.

Participants will perform the auditory lexical decision task on tablet devices using a previously developed app. They will first answer questions on their age, handedness, native languages, other spoken languages, age at which they began to learn English, English-speaking countries they have visited, and whether or not they grew up in western Canada. They will then hear a series of 200 stimuli and must mark whether they think each stimulus is a real or fictious word. There are a total of 2000 words split into 32 different lists. Participants will perform this task before commencing treatment (T0), after each stimulation session (T1-30), and 1 month after trial completion (T60).

There are 3 validated versions of the SCIP. To prevent participants from improving their scores by way of repeated exposure, version 1 will be administered at baseline, version 2 after the 30 treatments are delivered, and version 3 at the 1-month postcompletion assessment.

**Table 1 table1:** Schedule of assessments.

Assessment			Timepoint								
			Enrollment and baseline^a^		Treatment period^b^						Follow-up^c^
			T0		T1-9; T11-19; T21-29		T10; T20		T30		T60

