### Data Analysis and Sample Size Calculations

The primary and secondary efficacy outcomes will be analyzed using a mixed effects repeated measures ANOVA (analysis of variance), with the study group and time as fixed factors and participants as random factors, based on the intention to treat principle. Due to the wide variety of potential adverse events that can be captured, we will present this information as frequency data.

To detect a moderate effect size for the primary outcome, represented by a Cohen *f* of 0.25, with a power of 80% and significance ⍺=.05, we estimate that 60 participants will need to complete the protocol. This assumes a moderate correlation (*r*=0.3) between time points, using the power curves described in the textbook by Kirk [46]. As a study of this scope, in the ultraresistant MDD population, has not been performed before, we are unable to estimate the dropout rate. We plan to conduct an interim analysis after 30 participants complete the protocol. We will analyze the main effects of the treatment by presenting the significance of the time, treatment group, and interaction terms in the ANOVA. If there is a significant interaction, we will conduct posthoc comparisons between mean treatment and placebo outcome scores, at each time point, to characterize this effect further and will use the Tukey method to control the familywise error rate.

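### The only active-versus-sham MADRS contrast the protocol names is run only after a significant group-by-time interaction, a test that the stated sample size of 60 does not appear to be built on

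*Protocol article*

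**What the plan says.** The Outcomes section defines the primary endpoint: "The primary outcome will be the change on the MADRS". It names no visit. Under Data Analysis and Sample Size Calculations, the efficacy outcomes go into a mixed effects repeated measures ANOVA with group and time as fixed factors. The treatment effect is to be analysed by "presenting the significance of the time, treatment group, and interaction terms in the ANOVA". The next sentence adds the contrast and its condition: "If there is a significant interaction, we will conduct posthoc comparisons between mean treatment and placebo outcome scores, at each time point". Those comparisons are meant to describe the interaction in more detail and carry a Tukey adjustment.

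The same section sizes the trial for an effect "represented by a Cohen *f* of 0.25", "with a power of 80% and significance" of 0.05, giving 60 completers. "This assumes a moderate correlation (*r*=0.3) between time points". It does not say whether f refers to the group term or to the interaction.

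**The concern.** The effect of interest is how much more the MADRS falls on active than on sham stimulation. Under the stated rule, the only contrast that would show this by visit is computed if a 4-df omnibus test is significant. This has two consequences.

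- **Availability.** A trial with a significant group term and a non-significant interaction would claim benefit with no planned contrast at any visit. If both terms are non-significant, no planned interval shows which effects have been ruled out. The Introduction says it is unclear whether earlier null results in treatment-resistant patients reflect lack of efficacy or study design, and an interval is what would help to settle that.
- **Bias.** Estimates produced only after a significant test are a selected set and lie, on average, further from zero than the truth.

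This is a rule that the article states, not a detail that it leaves out. An analysis plan that followed the wording would inherit it.

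**Working it through.** **Inputs from the protocol article.** N = 60 completers, allocated 1:1, so 30 per arm; alpha 0.05; f = 0.25; r = 0.3. MADRS is measured at m = 5 visits (T0, T10, T20, T30, T60; Data Collection and Table 1). No MADRS SD is given, so results are in SD units.

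**Assumptions.** Equal variances and equal correlations across visits, complete data, no true difference at T0, and the effect profiles stated below.

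**Step 1: which term gives 60?**

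- Group main effect: λ = N f² m / (1 + (m−1)r) = 60 × 0.0625 × 5 / 2.2 = 8.52, df 1 and 58, power 0.819. Power of 80% needs N = 58. Counting only the 4 post-baseline visits: λ = 15 / 1.9 = 7.89, power 0.789, N = 62. Both are close to 60.
- Interaction: λ = N f² m / (1−r) = 18.75 / 0.7 = 26.8, df 4 and 232, power 0.99. Power of 80% needs N = 28 (32 with 4 visits).
- Other definitions of f for the interaction: λ = N m f² gives N = 40 (5 visits) or 46 (4 visits); λ = N f² / (1−r) gives 136 or 124.

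Only the group main effect reproduces 60.

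**Step 2: how often is the comparison triggered?** For group, f = 0.25 is a mean difference of 0.5 SD over five visits. With zero at T0 and a constant effect d afterwards, 4d/5 = 0.5, so d = 0.625 SD. For visit differences D, the interaction has λ = (30/2) Σ(D − mean D)² / (1−r).

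- Constant 0.625: Σ = 0.5² + 4 × 0.125² = 0.3125; λ = 15 × 0.3125 / 0.7 = 6.70; probability of significance 0.51.
- Constant 0.5: Σ = 0.4² + 4 × 0.1² = 0.20; λ = 4.29; probability 0.33.
- Constant 0.3: λ = 1.54; probability about 0.13-0.14.
- Even rise from T0 to 0.625 at T30, then held: λ = 6.32; probability 0.48. The same shape rising to 0.5: λ = 4.05; probability 0.32.

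In the constant 0.625 case the group test has power 0.819. The two F tests are almost independent here, so the group term alone is significant in about 0.819 × (1 − 0.51) = 0.40 of trials. Simulation gives 0.40-0.41.

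**Step 3: bias when triggered.** Simulation of the stated ANOVA, 30 per arm, r = 0.3. Each cell is the mean estimate given a significant interaction, divided by the true value.

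| Profile | T30 mean difference | Difference in change, T0 to T30 |
|---|---|---|
| Constant 0.625 SD | 1.05-1.06 | 1.27 |
| Constant 0.5 SD | 1.08-1.11 | 1.44-1.45 |
| Rise to 0.625 SD | 1.11 | 1.29 |
| Rise to 0.5 SD | 1.18-1.20 | 1.47-1.49 |

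The change contrast is inflated more because selection also favours a chance imbalance at T0: about −0.13 SD on average for constant 0.625, and −0.18 SD for constant 0.5.

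**Step 4: sensitivity to r.** With r = 0.7 and 0.625 SD, λ is 15 × 0.3125 / 0.3 = 15.6 for a constant effect and the trigger rate is 0.88-0.90 over the constant and rising profiles. Inflation falls to 1-3% (T30 difference) and 4-6% (change).

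**Step 5: precision without the condition.** With 60 completers the 95% CI half-width for the T30 difference is 2.00 × √(2/30) = 0.52 SD. For the difference in change it is 0.52 × √(2 × 0.7) = 0.61 SD. The estimate is available in every trial and free of this selection.

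**The case against.** A reader might infer that the trial will often report no effect size at all. The text does not support that. It makes post hoc comparisons conditional; it does not say that group means, model estimates or the group difference averaged over visits will be withheld. When the group term alone is significant, the fitted model still yields that averaged difference, although T0 dilutes it. The Strengths section also commits to CONSORT 2010, and an article may leave tabulated estimates to a fuller document. All of this stands. A general reporting pledge does not, however, cancel a specific conditional rule for the one named contrast.

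A reader might also apply the 27% and 45% to the visit differences. The conditional sentence speaks of mean outcome scores at each time point, and for those the inflation with a constant effect is about 5-9%. The larger figures belong to the change from baseline, which is how Outcomes defines the endpoint.

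Finally, the frequencies rest on assumed profiles. The plan fixes f, r and N but not the shape over visits or the term that f describes, and the power curves it cites are not shown. If f meant the interaction, power at 60 would be 0.99 under the usual formula and the condition would rarely fail; but that reading calls for 28 completers, not 60.

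**Conclusion.** The point holds in limited form. The only active-versus-sham MADRS contrast that the article names depends on a significant interaction, while the stated sample size matches the group main effect. At the plan's r of 0.3 and the effect that reproduces 60, the contrast is triggered in about half of trials, and in about one third at a true 0.5 SD. When triggered it is biased away from zero. The bias is modest for the T30 difference with a constant effect, about 19% with a gradual rise to 0.5 SD, and larger for change from baseline. These sizes assume no T0 difference, complete data and equal correlations, and they shrink markedly if r is near 0.7. The fault is conditioning the planned contrast on significance; the document does not support a claim that no effect size can be given.

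**What to change.** Remove the condition as far as estimation is concerned. State that the model-based active-minus-sham difference in MADRS change, with its 95% CI, will be reported whatever the interaction p-value. Prespecify one lead contrast (for example, change from T0 to T30) and give the other visits as supporting estimates.

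Do the same for QIDS-SR-16, WHODAS 2.0 and SCIP at their scheduled visits. For SCIP, first reconcile those visits: the Data Collection text describes three administrations (baseline, after 30 sessions, one month later), whereas Table 1 also ticks T10 and T20.

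If Tukey-adjusted post hoc tests are still wanted after a significant interaction, describe them separately, and say whether the reported intervals are adjusted.

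The cost is a sentence or two of protocol or analysis-plan wording. The model is already to be fitted, and no new data or participants are needed.

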## Methods

### Trial Design

The Neurostimulation of the Brain in Depression (NESBID) trial is a pragmatic, randomized, parallel group, participant- and investigator-blinded multicenter superiority trial. Participants will be randomized in a 1:1 fashion between active and sham tDCS and will continue to receive their usual treatment, including pharmacological and psychological therapies, during the course of the trial.

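### The Tukey method named for the per-visit active-versus-sham comparisons does not fit them: within a visit it adjusts nothing, and across all ten group-by-visit means it is far stricter than needed

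*Protocol article*

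**What the plan says.** The protocol article (Data Analysis and Sample Size Calculations) fits a repeated measures ANOVA with group and time as fixed factors and participant as a random factor. It then sets a conditional second step: "If there is a significant interaction, we will conduct posthoc comparisons between mean treatment and placebo outcome scores, at each time point". For these comparisons the investigators "will use the Tukey method to control the familywise error rate". The set of means to which Tukey is to be applied is not stated.

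Two other sections fix the number of comparisons. Trial Design has two arms: "Participants will be randomized in a 1:1 fashion between active and sham tDCS". Data Collection schedules measurements "at the beginning of the trial (T0), after every 10 sessions (T10, T20, and T30") "and 1 month after trial completion (T60; Table 1"), and Table 1 shows the MADRS at all five of these visits across its two rows. The comparisons described are therefore five active-versus-sham contrasts, one of them at baseline.

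**The concern.** Tukey's procedure controls the error over every pairwise difference among k means. The plan does not want every pairwise difference. It wants one difference, active minus sham, repeated across visits. The multiplicity lies across visits, and Tukey can be attached to this layout in only two natural ways:

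- **Within each visit**, k = 2. There is one pair, so there is nothing to adjust, and the number of visits never enters.
- **Across all group-by-visit cells**, k = 10. The family then includes comparisons nobody asked for, such as active at T10 against sham at T60.

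These contrasts are how the article proposes to show when active tDCS differs from sham. Two analysts following the same sentence could use a critical t of 1.97 or of 3.20 and report opposite findings at a visit from the same data. The wording also takes in T0, which precedes treatment, so any difference there is chance.

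**Working it through.** **Inputs from the protocol.** Two arms, 1:1; 60 completers, so 30 per arm; five visits; r = 0.3 between time points; effect "represented by a Cohen *f* of 0.25"; and "with a power of 80% and significance ⍺=.05". For two equal groups d = 2f = 0.5 SD.

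**Assumptions added here.** Equal SD and equal correlation across visits, no dropout, two-sided pairwise tests. The effects of 0.74 and 1.0 SD are illustrations and do not come from the protocol; 0.74 SD is about what an unadjusted single-visit test with 30 per arm detects with 80% power.

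**1. The protocol's own figure.** For the group main effect over m visits, λ = f²·N·m / (1 + (m − 1)r), with 1 and N − 2 df.
- m = 5, N = 60: λ = 0.0625 × 60 × 5 / 2.2 = 8.52; power 81.9%; 80% is reached at N = 58.
- m = 4, N = 60: λ = 0.0625 × 60 × 4 / 1.9 = 7.89; power 78.9%; 80% is reached at N = 62.

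The stated 60 is thus reproduced as a test of the group main effect. It does not depend on the post hoc contrasts.

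**2. Critical values.** The Tukey critical t is q(0.95; k, df)/√2, with residual df = (60 − 2) × (5 − 1) = 232.

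| Procedure | Comparisons covered | Critical t |
|---|---|---|
| Unadjusted t | 1 | 1.970 |
| Tukey, k = 2 (within a visit) | 1 | 1.970 |
| Bonferroni, four visits | 4 | 2.517 |
| Bonferroni, five visits | 5 | 2.597 |
| Tukey, k = 10 (all cells) | 10 × 9 / 2 = 45 | 3.195 |

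With the single-visit df of 58 the pattern is the same: 2.002 for both the unadjusted test and k = 2, and 3.290 for k = 10.

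**3. Within-visit reading: error.** The stated sequence was simulated with 30 per arm and r = 0.3: interaction F test at 0.05, then, if significant, unadjusted t tests at all five visits. The event counted is that the interaction is significant and at least one visit with no true difference is declared different.

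| True effect | Probability |
|---|---|
| None at any visit | 3.8 to 3.9% |
| 0.74 SD at T30 only | 13.7% |
| 1.0 SD at T30 only | 16.5% |
| 0.5 SD at T30 and T60 | about 9% |
| 0.74 SD at T30 and T60 | about 12% |
| 1.0 SD at T30 and T60 | 13.7% |
| Effect builds from T10, only T0 null | about 3% |

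Without the interaction requirement, and with no effect at any visit, the figure over five visits would be about 21%.

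**4. Ten-cell reading: error and power.** The familywise error over the five wanted contrasts is about 0.9%, against the 5% allowed. Per-visit power comes from a noncentral t with noncentrality d × √(30/2) and 232 df.

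| d | Noncentrality | Tukey, ten cells | Bonferroni, four visits |
|---|---|---|---|
| 0.5 (protocol's f = 0.25) | 1.94 | 11% | 28% |
| 0.74 (assumed) | 2.87 | 37% | 64% |

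The loss against Bonferroni over four visits is 17 percentage points at d = 0.5 and 27 points at d = 0.74.

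**The case against.** The strongest reply is that the comparisons are made only after a significant interaction. A reader might infer from the two-group result that the trial runs a 21% familywise error. The protocol does not support that. The 21% belongs to a procedure without the interaction test, and with no effect at any visit the planned sequence stays near 4%. It also stays low when the effect builds from T10 and only T0 is null. What remains is the case where the effect is present at some visits and absent at others. The interaction test then passes because of the real effect and no longer protects the null visits. That is the pattern these comparisons are meant to describe.

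Second, Tukey over all ten cells does keep the error below 5%, so it is conservative and not invalid. That is correct. A reader might also infer a fixed loss of about half the power. The loss has no single size: it depends on the effect and on the comparator, and the document supports only the calculation at its own d = 0.5.

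Third, an article may leave the contrast family to a fuller analysis plan. That would answer a complaint that the family is unstated. Here, however, the article names a method and what it is to achieve, and the method suits neither reading of the comparisons it is attached to.

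Fourth, the consequence is limited. The contrasts are post hoc and follow the omnibus test. This stands and limits the severity. Nor does the text establish that raw scores would be compared in place of change, so no point is made of that.

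**Conclusion.** The point holds, with minor to moderate severity. Tukey does not suit one active-versus-sham contrast per visit. Read within a visit, it is the unadjusted t test. The promised control then rests wholly on the interaction test, which gives about 4% when there is no effect anywhere but about 12 to 17% when an assumed effect of 0.74 to 1.0 SD is at T30 only, or one of 0.74 SD is at T30 and T60. Read over ten cells, control is delivered at an avoidable price: per-visit power of 11% against 28% for Bonferroni over four visits at the protocol's own effect, and 37% against 64% at an assumed 0.74 SD.

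These figures assume 30 completers per arm, r = 0.3 between all visits, equal SDs and two-sided tests. The protocol gives no dropout estimate, and fewer completers would lower both power columns. Nothing here bears on the omnibus ANOVA tests or on the target of 60.

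**What to change.** Replace the Tukey sentence with one that names the family and a method suited to it: if the interaction is significant, estimate the active-minus-sham contrasts at T10, T20, T30 and T60 from the mixed model and adjust these four by Holm (or Bonferroni). Leave out the T0 comparison, where no treatment effect can exist. The interaction requirement may stay, because Holm or Bonferroni over the four contrasts controls the error with or without it.

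The cost is one sentence of analysis wording. It needs no new data, no further participants, and no change to the primary test.

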## Results

The trial has received approval from the University of Alberta Research Ethics Board and is registered on ClinicalTrials.gov (NCT04159012). We had planned to begin recruiting participants in 2019; however, all in-person research activities have since been suspended due to the COVID-19 pandemic and its physical-distancing implications. We anticipate that participant recruitment will begin in June 2021 at the Grey Nuns Hospital, with recruitment at the University of Alberta Hospital to begin thereafter. The trial is expected to run until June 2022.

## Discussion

### Study Overview

In this multicenter, double-blinded, randomized controlled trial, we aim to determine the effectiveness of tDCS in ameliorating ultratreatment-resistant MDD, operationally defined as depression that has failed to remit despite the previous use of at least five antidepressants at effective doses, ketamine, or ECT. In addition to their usual treatment, participants will be randomly assigned to receive either 30 weekday sessions of active (2 mA) or sham tDCS, with the anode over the left DLPFC and the cathode over the right DLPFC. We will regularly assess depression severity and functional impact using the MADRS, QIDS-SR-16, and WHODAS 2.0, throughout the trial and 1 month after study completion. We will assess cognitive changes using the SCIP. We will also regularly assess treatment-related side effects using validated scales.

As depression is known to affect speech [47-49], a parallel component of the study will examine how participant speech and auditory lexical decision changes throughout the trial period. Entrance and exit interviews will be recorded, transcribed (with identifying information removed), and analyzed by collaborators in the Department of Linguistics at the University of Alberta. Participant accuracy and response latency on the auditory lexical decision task will be similarly evaluated and compared.

